# Lomustine with or without reirradiation for first progression of glioblastoma, LEGATO, EORTC-2227-BTG: study protocol for a randomized phase III study

**DOI:** 10.1186/s13063-024-08213-7

**Published:** 2024-06-07

**Keywords:** Glioblastoma, Progression, Lomustine, Reirradiation, LEGATO, Randomized controlled trial

## Abstract

**Background:**

Chemotherapy with lomustine is widely considered as standard treatment option for progressive glioblastoma. The value of adding radiotherapy to second-line chemotherapy is not known.

**Methods:**

EORTC-2227-BTG (LEGATO, NCT05904119) is an investigator-initiated, pragmatic (PRECIS-2 score: 34 out of 45), randomized, multicenter phase III trial in patients with first progression of glioblastoma. A total of 411 patients will be randomized in a 1:1 ratio to lomustine (110 mg/m^2^ every 6 weeks) or lomustine (110 mg/m^2^ every 6weeks) plus radiotherapy (35 Gy in 10 fractions). Main eligibility criteria include histologic confirmation of glioblastoma, isocitrate dehydrogenase gene (*IDH*) wild-type per WHO 2021 classification, first progression at least 6 months after the end of prior radiotherapy, radiologically measurable disease according to RANO criteria with a maximum tumor diameter of 5 cm, and WHO performance status of 0–2. The primary efficacy endpoint is overall survival (OS) and secondary endpoints include progression-free survival, response rate, neurocognitive function, health-related quality of life, and health economic parameters. LEGATO is funded by the European Union’s Horizon Europe Research program, was activated in March 2024 and will enroll patients in 43 sites in 11 countries across Europe with study completion projected in 2028.

**Discussion:**

EORTC-2227-BTG (LEGATO) is a publicly funded pragmatic phase III trial designed to clarify the efficacy of adding reirradiation to chemotherapy with lomustine for the treatment of patients with first progression of glioblastoma.

**Trial registration:**

ClinicalTrials.gov NCT05904119. Registered before start of inclusion, 23 May 2023

**Supplementary Information:**

The online version contains supplementary material available at 10.1186/s13063-024-08213-7.

## Background

Glioblastoma is the most common primary malignant brain tumor of adults and has a fatal prognosis. Following standard first-line therapy consisting of biopsy or maximal safe neurosurgical resection followed by radiotherapy and chemotherapy with temozolomide with or without tumor-treating fields, practically all patients experience tumor progression or recurrence and further treatment lines are required [1]. Therapeutic options at second line include resection, chemotherapy, radiotherapy, experimental treatment, and best supportive care. Targeted pharmacotherapy, e.g., with specific BRAF or NTRK inhibitors, is applicable only in a minority of patients in whom druggable molecular alterations are detected [1].

Despite the fact that class I evidence is lacking, chemotherapy with lomustine is widely considered a standard treatment option at first progression of glioblastoma and has been used as comparator therapy on the control arm of several contemporary randomized clinical trials [1, 2]. Reirradiation is commonly used as a treatment option for recurrent glioblastoma in clinical routine, although there are very limited prospective data [3–5]. A number of small studies documented a favorable safety profile for reirradiation delivered in different regimens and with or without various chemotherapies [3, 4, 6–13]. High level of evidence data on efficacy and impact on the neurological status and quality of life are lacking.

EORTC-2227-BTG (LEGATO, NCT05904119) was designed as pragmatic clinical trial (PRECIS-2 score: 34 out of 45 as defined by EORTC headquarters using http://precis-2.org, Table 1) [14] to test the hypothesis that the addition of radiotherapy to lomustine chemotherapy is beneficial for the treatment of progressive glioblastoma. This trial is funded by the European Union’s Horizon Europe Research program (project number: 101103655, [contact]). This is an investigator-initiated clinical trial. Therefore, the funders played no role in the design of the study and collection, analysis, and interpretation of data and in writing the manuscript. Here, we summarize the clinical trial design of this ongoing study with first site activation achieved in March 2024 and a projected study completion by 2028.

**Table 1 Tab1:** PRECIS-2 scoring of the LEGATO trial. *1* very explanatory, *2* rather explanatory, *3* equally explanatory and pragmatic, *4* rather pragmatic, and *5* very pragmatic

PRECIS-2 domain	Rating
Eligibility	2
Recruitment	4
Setting	5
Organization	3
Fexibility in treatment delivery	4
Flexibility in adherence	4
Follow-up	2
Primary outcome	5
Primary analysis	5
Total	34

## Study design

EORTC-2227-BTG (LEGATO, NCT05904119) is an investigator-initiated, pragmatic, randomized, open-label, multicenter phase III trial in patients with first progression of glioblastoma. Figure 1 summarizes the study design. Of note, the information provided reflects the protocol version 3.0 approved on 24 January 2024. Investigators must refer to the latest version of the full study protocol, which is available to study investigators in their trial files. Publicly available information and updates on the trial progress can be found at https://legato-horizon.eu.

**Fig. 1 Fig1:**
[figure not shown]
Study scheme of the EORTC-2227-BTG (LEGATO) trial

### Trial population

Main eligibility criteria include age ≥18 years, written informed consent, histologic confirmation of glioblastoma, IDH wild-type per WHO 2021 classification, first progression or recurrence after first-line treatment with biopsy or maximal safe resection and standard radiotherapy or chemoradiotherapy having occurred at least 6 months after the end of prior radiotherapy, radiologically measurable disease according to RANO criteria with a maximum tumor diameter of 5 cm, WHO performance status of 0–2, and any *MGMT* promoter methylation status. The detailed eligibility criteria are shown in Table 2. The patients will receive extensive information about the study set-up and requirements during the recruitment by the local investigators, who are board-certified physicians with current good clinical practice (GCP) certification and confirmed delegation and completed training for clinical trial activities. The importance of completion of the follow-up will be stressed. A clinical trial insurance has been taken out according to the laws of the countries where the study will be conducted.

**Table 2 Tab2:** Eligibility criteria for the EORTC-2227-BTG (LEGATO) trial.

Inclusion criteria	Comment	Exclusion criteria
Before patient’s enrolment, written informed consent must be given according to ICH/GCP, and national/local regulations.		Any prior anticancer treatment for recurrent glioblastoma (except surgery).
Patients with first progression or recurrent glioblastoma after first-line treatment with biopsy or maximal safe resection and standard radiotherapy or chemoradiotherapy having occurred at least 6 months after the end of prior radiotherapy.	Prior first-line therapy may include any systemic antineoplastic treatment other than nitroureas, tumor-treating fields, conventionally fractionated or abbreviated (minimum 15 fractions) radiotherapy.	Significant reduction in thrombocyte and/or leukocyte counts (leukocytes < 4000/mm*3* and/or the platelets < 100,000/mm3) as well as severe renal impairment according to investigator's opinion.
Measurable disease according to RANO criteria with a maximum tumor diameter of 5 cm (local investigator assessment).	In case of multiple lesions, maximum cumulative CTV diameter of 5 cm treatable by one isocenter.	Previous (last dose in the 15 days prior to lomustine initiation) or ongoing salicylates due to increased risk of bleeding in case of thrombocytopenia.
Candidates for treatment with lomustine as per physician’s assessment.		History or present acute leukemia or any myeloid disease.
In case of surgery for recurrence: fully recovered from surgery, confirmation of recurrence by histology, and patient fit for treatment as per local investigator assessment.		Known hypersensitivity to the active components or excipients of lomustine.
Histologically proven diagnosis of glioblastoma, IDH wild-type per WHO 2021 classification and local assessment of tissue from diagnosis or recurrence.		Concurrent or recent history (30 days prior to lomustine initiation) of varicella (infection or exposure) and herpes zoster.
Stable or decreasing dose of steroids for 7 days prior to enrolment		Known hereditary galactose intolerance, Lapp-lactase deficiency, or glucose-galactose malabsorption.
Age ≥ 18 years		Known coeliac disease or wheat allergy.
WHO performance status of 0–2		Patients with pulmonary infiltration, interstitial pneumonia, or pulmonary fibrosis and with a baseline below 70% of the predicted FVC or DLCO.
Women of childbearing potential must have a negative serum pregnancy test within 7 days prior to the first dose of study treatment.		Live attenuated vaccine in the 3 months prior to lomustine initiation.
Patients of childbearing/reproductive potential must agree to use adequate birth control measures during the study treatment period and for at least 6 months after the last dose of study treatment. A highly effective method of birth control is defined as a method which results in a low failure rate (i.e., less than 1% per year) when used consistently and correctly.		Any serious or uncontrolled medical condition (e.g., infections, chronic alcoholism, drug addiction) or abnormality, in the judgment of the investigator that prohibits obtaining informed consent, safe participation, and study completion.
Female subjects who are breastfeeding should discontinue nursing prior to the first dose of study treatment and until 6 months after the last study treatment.		Known contraindication to imaging tracer or any product of contrast media and MRI contraindications.
Non-sterile males must use contraception during treatment and for 6 months after the last dose.		Any psychological, familial, sociological, or geographical condition potentially hampering compliance with the study protocol and follow-up schedule; those conditions should be assessed and discussed with the patient before the enrolment in the trial.
Non-sterile males must avoid sperm donation for the duration of the study and for at least 6 months after the last dose of study treatment.		

*DLCO* Carbon monoxide diffusing capacity, *FVC* Forced vital capacity, *GCP* Good clinical practice, *ICH* International Council of Harmonization, *IDH* Isocitrate dehydrogenase gene, *MRI* Magnetic resonance imaging, *RANO* Response Assessment in Neuro-Oncology, *WHO* World Health Organization

### Objectives and endpoints

The objectives and endpoints of the LEGATO trial are detailed in Table 3. In brief, the primary efficacy endpoint is overall survival (OS) and secondary endpoints include progression-free survival (PFS), response rate, neurocognitive function, health-related quality of life, and health economic parameters.

**Table 3 Tab3:** Objectives and endpoints of the EORTC-2227-BTG (LEGATO) trial

**Objectives**	**Endpoints**
**Primary objective**	**Primary endpoint**
To show that lomustine and radiotherapy improves overall survival in the study population as compared to standard treatment.	Overall survival from the date of enrolment.
**Secondary objectives**	**Secondary endpoint**
To show that lomustine and radiotherapy improves progression-free survival in the study population as compared to standard treatment.	Progression-free survival from enrolment per RANO criteria as assessed by the local investigator.
To show that lomustine and radiotherapy improves response in the study population as compared to standard treatment.	Objective response per RANO criteria as assessed by the local investigator.
To assess the toxicity profile of lomustine plus reirradiation.	Safety according to the CTCAE 5.0.
To assess whether lomustine plus reirradiation improves QDFS as compared to lomustine alone. To assess the difference in secondary and exploratory QoL scales between lomustine plus reirradiation and lomustine alone.	QDFS survival defined as a deterioration event of ≥10-point worsening from baseline in the GHQ without further improvement (i.e., no subsequent ≥ 10-point improvement) or death due to any cause while on treatment
To assess patient’s neurocognitive functioning with lomustine plus reirradiation.	Patient’s neurocognitive functioning assessed by MMSE.
To assess health economics with lomustine plus reirradiation.	Health utility values

*CTCAE* Common Terminology Criteria of Adverse Events, *GHQ* General health questionnaire, *MMSE* Mini mental state exam, *QDFS* Quality of live deterioration free survival, *QoL* Quality of life, *RANO* Response Assessment in Neuro-Oncology

OS is defined as the number of days from the date of enrolment to the date of death due to any cause. If a subject has not died, the data will be censored at the last date documented to be alive. PFS will be defined as the number of days from the date of enrolment to the date of earliest radiological disease progression or to the date of death due to any cause, if disease progression did not occur. Patients for whom neither death nor progression have been documented will be censored at the date of the last radiological assessment that the patient was progression-free.

Radiological follow-up for the evaluation of PFS and response rate will be performed by cranial MRI every 12 weeks. MRI will be assessed according to Response Assessment in Neuro Oncology (RANO) criteria interpretation by the local investigator.

Toxicity reporting will be done according to the Common Terminology Criteria for Adverse Events (CTCAE) version 5.0. Neurocognitive functioning will be assessed using Mini-Mental State Examination (MMSE) every 6 weeks and the NANO scale will be utilized for evaluation of neurological function. Health-related Quality of Life (HRQoL) will be assessed every 6 weeks using EORTC Quality of Life Questionnaire (QLQ)-C30, QLQ-BN20 Brain tumor module and one additional item from the EORTC Item Library (IL)-46.

Self-reported HRQoL data will be transformed into health utility values for subsequent health economic analyses. To this end, the EORTC QLQ-C30 data collected for each study subject and at each HRQoL assessment time point will be mapped to health utility values using an established indirect mapping approach [15, 16]. In the adopted indirect mapping approach, first the probabilities of belonging to European Quality-of-Life-5 Dimensions (EQ-5D) categories will be calculated, and then the corresponding EQ-5D scores will be translated into health utility values using a country-specific value set for the conversion [16].

Tables 4, 5, and 6 summarize study calendar before treatment start, during treatment, and during follow-up. Data will be captured in electronic case report forms.

**Table 4 Tab4:** Study calendar—before treatment started

Assessment	Within 14 days prior to enrolment	Within 7 days prior to enrolment
Disease evaluation (cMRI)	X	
Complete medical history	X	
Concomitant medication		X
Vital signs		X
ECOG/WHO performance status		X
Clinical examination		X
Pulmonary function test		X
Mini-Mental State Examination (MMSE)		X
NANO scale		X
12-lead ECG		X
Hematology		X
Serum chemistry		X
Coagulation		X
Pregnancy test for WOCBP		X
Health-related quality of life (HRQoL)		X
Elderly Minimal Dataset Comprehensive Geriatric Assessment (G8) for patients ≥ 70 years of age		X

*cMRI* contrast magnetic resonance imaging, *ECOG/WHO* Eastern Cooperative Oncology Group/World Health organization, *MMSE* Mini Mental State Examination, *NANO* Neurologic Assessment in Neuro-Oncology, *ECG* Electrocardiogram, *WOCBP* Women of childbearing potential, *HRQoL* Health-related quality of life

**Table 5 Tab5:** Study calendar—during protocol treatment

Assessment	End of RT	Every 6 weeks	Days 28 and 35 of each 6-week cycle	Every 12 weeks	End of study treatment
	Experimental arm only	Both treatment arms	Both treatment arms	Both treatment arms	30 (± 7 days) after last dose
Disease evaluation (cMRI)				X	
Assessments of adverse events	X	X			X
Concomitant medication		X			X
Vital signs		X			X
ECOG/WHO performance status	X	X			X
Clinical examination		X			X
Pulmonary function test		X			X
Mini-Mental State Examination (MMSE)		X			X
NANO scale		X (optional)			X (mandatory)
12-lead ECG					X
Hematology		X	X		X
Serum chemistry		X			X
Coagulation		X			X
Pregnancy test for WOCBP		X			X
Health-related Quality of Life (HRQoL)		X			X

*RT* radiotherapy, *cMRI* contrast magnetic resonance imaging, *ECOG/WHO* Eastern Cooperative Oncology Group/World Health organization, *MMSE* Mini Mental State Examination, *NANO* Neurologic Assessment in Neuro-Oncology, *ECG* electrocardiogram, *WOCBP* women of childbearing potential, *HRQoL* health-related quality of life

**Table 6 Tab6:** Study calendar—follow-up

**Assessment**	**Absence of disease progression**	**Disease progression**

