	**Every 12 weeks ± 14 days after last treatment administration**	
Survival status	X	X
Diagnosis of new malignancy	X	X
Subsequent anti-cancer therapy	X	X
Pregnancy test for WOCBP	Pregnancy test is to be renewed/repeated for 6 months after last protocol treatment	
Health-related quality of life (HRQoL)	X	X
Disease evaluation (cMRI)	X	

*WOCBP* Women of childbearing potential, *HRQoL* Health-related quality of life, *cMRI* Contrast magnetic resonance imaging

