#### Control arm: lomustine

In the control arm, lomustine will be given at a recommended dose of 110 mg/m^2^ (maximum absolute dose 200 mg, minimum dose 80 mg) every 6 weeks. The maximum cumulative dose must not exceed 1000 mg/m^2^ to prevent pulmonary toxicity [19]. Participants must start lomustine within 7 days of enrolment. Treatment will be administered until disease progression, unacceptable toxicity, death, or until the occurrence of any predefined withdrawal criterion such as withdrawal of patient consent or safety concerns. Lomustine has a well-known safety profile that includes fatigue, hematological symptoms, and on rare occasions, the development of pulmonary toxicity after more than 6 months of treatment and a cumulative dose of 1000 mg/m^2^. Hematological toxicity, as the main concern in the treatment by lomustine occurs usually after 4 weeks after drug administration. Recommendations for dose modifications follow published guidelines [20].

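### QDFS counts a death only if it occurs on treatment, so known deaths are left out according to a post-randomisation event

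*Protocol article*

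**What the plan says.** In the protocol article, Table 3 (Objectives and endpoints) sets a between-arm objective: "To assess whether lomustine plus reirradiation improves QDFS as compared to lomustine alone". The footnote expands QDFS as "Quality of live deterioration free survival". An event is a lasting worsening of at least 10 points from baseline, "or death due to any cause while on treatment". The scale is given as GHQ, expanded as "General health questionnaire".

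The text after Table 3 defines OS and PFS from enrolment, and both count death from any cause with no on-treatment limit. It lists the quality-of-life instruments as the EORTC "Quality of Life Questionnaire (QLQ)-C30, QLQ-BN20 Brain tumor module and one additional item" from the EORTC Item Library.

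Under Control arm: lomustine, "Treatment will be administered until disease progression, unacceptable toxicity, death, or until the occurrence of any predefined withdrawal criterion". There is also a ceiling: "The maximum cumulative dose must not exceed 1000 mg/m^2^ to prevent pulmonary toxicity". The experimental arm uses the same lomustine regimen.

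Table 5 schedules quality of life every 6 weeks on treatment. Table 6 schedules survival status and quality of life, with and without progression, "Every 12 weeks ± 14 days after last treatment administration".

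**The concern.** An endpoint named as survival free of deterioration should fail at death. Here a patient who progresses, stops lomustine and dies without a recorded deterioration never has an event, although Table 6 ensures that the death is known. Stopping happens after randomisation and is tied to progression, which the trial hopes radiotherapy will delay. Which deaths count can therefore differ between arms for reasons other than quality of life or survival.

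The comparison at stake is the one meant to show whether adding radiotherapy preserves quality of life. It could show a difference that comes only from unequal time on lomustine, or miss a real one.

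**Working it through.** **Inputs from the article.** Median OS 9 v 12.5 months; hazard ratio 0.72; one-sided 2.5%; power 80%; interim at 97 OS events (33%); lomustine 110 mg/m² every 6 weeks; cumulative limit 1000 mg/m².

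**Assumed, because not stated.** Median time to stopping treatment, median time to deterioration, and exponential times.

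**The plan's own figures.** 9/12.5 = 0.72. Events by Schoenfeld's formula: 4 × (1.960 + 0.842)² / (ln 0.72)² = 291, and 97/291 = 33.3%. The OS design reproduces. The article gives no figure for QDFS.

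**1. Share of deaths on treatment.** The limit allows 1000/110 = 9 full cycles = 54 weeks = 12.4 months. With l = ln 2/median OS and m = ln 2/median time to stopping, the share is l/(l+m) × (1 − e^(−12.4(l+m))).

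| Median time to stopping (months) | 1.5 | 3 | 4.5 | 6 | 9 |
|---|---|---|---|---|---|
| OS median 9 | 14% | 24% | 31% | 36% | 43% |
| OS median 12.5 | 11% | 19% | 25% | 29% | 34% |

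So 57 to 89% of deaths fall off treatment. Even if nobody stopped before 12.4 months, 2^(−12.4/9) = 38% and 2^(−12.4/12.5) = 50% would still be alive then.

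**2. Deaths that would be the first event.** A death after a counted deterioration loses nothing, so this is the relevant group. With d = ln 2/median time to deterioration, and independent times, the uncounted share is m/(l+d+m), ignoring the dose limit. In units of 1/median, with OS median 9:
- stopping 6, deterioration 6: 0.1667/(0.1111 + 0.1667 + 0.1667) = 38%
- stopping 3, deterioration 6: 0.3333/(0.1111 + 0.1667 + 0.3333) = 55%
- stopping 2, deterioration 12: 0.5/(0.1111 + 0.0833 + 0.5) = 72%, or 69% in simulation with follow-up cut at 5 to 38 months

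**3. Hazard ratio when the arms do not differ.** Death (median 9 months) and deterioration have identical hazards in both arms; only time on treatment differs. If off-treatment deaths are censored, the QDFS hazard at time t is d + l·e^(−mt), which is higher in the arm with the smaller m. For stopping medians 3 v 6 and deterioration 12, the ratio at 3 months is (0.0833 + 0.1111 × 0.707)/(0.0833 + 0.1111 × 0.5) = 1.17. Cox estimates over follow-up (20,000 per arm, 36-month cutoff, simulation error about 0.01 to 0.02), longer-treated arm against the other:

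| Stopping medians | Deterioration median | All deaths counted | Off-treatment deaths censored | Off-treatment deaths ignored, patient stays event-free | Whole endpoint censored at end of treatment |
|---|---|---|---|---|---|
| 3 v 4.5 | 6 | 0.99 | 1.06 | 1.08 | 0.99 |
| 3 v 4.5 | 12 | 1.00 | 1.08 | 1.14 | 1.02 |
| 3 v 6 | 6 | 0.99 | 1.10 | 1.19 | 0.99 |
| 3 v 6 | 12 | 1.01 | 1.13 | 1.23 | 1.03 |
| 2 v 4 | 6 | 0.99 | 1.10 | 1.18 | 1.01 |
| 2 v 4 | 12 | 1.00 | 1.15 | 1.26 | 1.00 |

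A separate run (40,000 per arm, deterioration medians 9 to 18) gave 1.09 to 1.17 with off-treatment deaths censored. Reversing the durations to 5 v 3 months gives about 0.90 to 0.92.

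**4. Death hazard higher after stopping.** Stopping medians 3 v 6, deterioration 6; resulting OS medians about 9.3 and 11.6 months. With all deaths counted the hazard ratio is 0.92. It becomes 0.99 with the whole endpoint censored at end of treatment, 1.02 with off-treatment deaths censored, and 1.15 with them ignored. At the 3-month stopping median, about 80% of first-event deaths go uncounted.

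**The case against.** **The phrase may limit the whole endpoint.** It closes the definition and can be read as governing deterioration as well as death. QDFS is then an on-treatment endpoint, and the null hazard ratio returns to about 1.00. This stands: the spurious difference belongs to one reading. The alternative is still unsound. It censors patients at progression, when prognosis worsens, and leaves the Table 6 quality-of-life data unused; in step 4 it turned 0.92 into 0.99.

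**The censoring rule may be elsewhere.** The article gives none for QDFS, and the full protocol may. That absence is not the point here. The point is the event definition, which the article does state.

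**A reader might infer a penalty on the radiotherapy arm.** The documents do not support that. They give neither time on treatment nor median PFS for either arm. The radiotherapy arm is the longer-treated one only if radiotherapy delays progression as hoped; if it stops lomustine earlier, the sign reverses. Step 3 also assumes 1.5 to 2 times the treatment time with no change in death or deterioration, and stopping independent of both.

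**A reader might infer that most deaths drop out of QDFS.** Most deaths are ineligible, but those preceded by a counted deterioration cost nothing. The first-event shares in step 2 are the right measure.

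**Secondary status.** QDFS is not primary, which limits the severity.

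**Conclusion.** The definition is faulty on either reading. It makes the counting of known deaths depend on stopping treatment, unlike OS and PFS in the same article. Under equal hazards roughly 38 to 69% of deaths that would be the first event go uncounted, and up to about 80% if the death hazard rises after stopping.

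If deterioration still counts in follow-up, the null hazard ratio is about 1.06 to 1.17 against the longer-treated arm with off-treatment deaths censored, and about 1.08 to 1.26 with them ignored. If the phrase limits everything, the ratio is about 1.00 and the fault is informative censoring. These sizes rest on assumed treatment and deterioration times; the direction between the arms is not documented.

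The scale name is a separate, smaller error: no instrument of that name is among those collected.

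The primary OS analysis, its 291 or so events and the 411 patients are unaffected. The point should be fixed, but the trial's main conclusion does not turn on it.

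**What to change.** Delete the on-treatment limit. Define QDFS as time from enrolment, as for OS and PFS, to the first definitive worsening of at least 10 points or death from any cause at any time, using both on-treatment and follow-up quality-of-life forms. Keep any on-treatment version as supportive only, with its censoring rule stated.

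Replace GHQ and its expansion, in Table 3 and the abbreviation list, with the collected scale that is intended, presumably the QLQ-C30 global health status/QoL scale. The sponsor should confirm this.

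The step from 6-weekly to 12-weekly assessment also makes detection of deterioration depend on time on treatment. A common 12-weekly grid would not solve this, because follow-up visits are timed from each patient's last treatment. A sensitivity analysis with interval-censored deterioration times can.

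The cost is wording in the protocol and analysis plan plus one sensitivity analysis. Tables 5 and 6 already collect the data. Make the change before outcome data are examined, since the trial is open-label and its analysts are not blinded.

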The main toxicity expected from re-irradiation is radionecrosis in less than 10% of cases. The increased, synergistic, risk of hematological toxicity in the combination of lomustine and reirradiation is expected to be minimal.

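### The follow-up calendar schedules no adverse-event assessment after 30 (±7) days from last dose, so late radionecrosis may be under-ascertained, most of all in patients who stop lomustine early

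*Protocol article*

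**What the plan says.** - **Objective.** Protocol article, Objectives and endpoints, Table 3 lists as a secondary objective: "To assess the toxicity profile of lomustine plus reirradiation". The endpoint is safety by CTCAE 5.0.
- **Expected harm.** The section on the experimental arm states: "The main toxicity expected from re-irradiation is radionecrosis in less than 10% of cases". It gives no time to onset.
- **On treatment.** In Table 5 the row "Assessments of adverse events" is marked at the end of radiotherapy (experimental arm only), every 6 weeks (both arms), and at the end-of-study-treatment visit, timed "30 (± 7 days) after last dose". No later adverse-event assessment is scheduled.
- **Follow-up.** Table 6, headed "Every 12 weeks ± 14 days after last treatment administration", lists survival status, new malignancy, subsequent anti-cancer therapy, pregnancy test, HRQoL and cMRI. The cMRI is marked only for patients without progression. There is no adverse-event row.
- **Duration of treatment.** For lomustine: "Treatment will be administered until disease progression, unacceptable toxicity, death", or a withdrawal criterion; also "The maximum cumulative dose must not exceed 1000 mg/m^2". Radiotherapy takes 2 weeks and is to start within 14 days of randomisation and/or within 7 days of the first lomustine intake.

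**The concern.** Radiotherapy is the randomised addition, and its toxicity is what the safety objective has to describe. The end of scheduled observation is tied not to radiotherapy but to the last dose of a drug whose duration varies from patient to patient. Two patients given identical radiotherapy can be observed for its effects for a few weeks or for nearly a year, depending on when lomustine stops.

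Table 6 does retain one late-harm item, new malignancy, but not the toxicity that the article itself calls the main one. If some radionecrosis appears only after the closing visit, the reported rate will be too low. Should the trial show a survival benefit, that rate is the harm figure that clinicians would weigh against it.

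**Working it through.** **1. What is scheduled, and for how long.** The plan states no length for adverse-event observation after radiotherapy, so there is no figure to reproduce. It can be derived from the calendar.

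- Full-dose cycles allowed by the cumulative limit: 1000 / 110 = 9.09, so at most 9.
- With 6-week cycles and no delay, dose k falls on day 42 × (k − 1) after the first lomustine dose.
- The closing visit falls 23 to 37 days after that.
- Radiotherapy starting on day 0 to 7 and lasting 2 weeks ends between about day 11 (start day 0, ten weekday fractions) and day 20 (start day 7).
- Shortest window after radiotherapy = 42(k − 1) + 23 − 20. Longest = 42(k − 1) + 37 − 11.

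| Lomustine doses | Last dose, day | Window after end of radiotherapy, days |
|---|---|---|
| 1 | 0 | 3 to 26 |
| 2 | 42 | 45 to 68 |
| 3 | 84 | 87 to 110 |
| 6 | 210 | 213 to 236 |
| 9 | 336 | 339 to 362 |

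**2. What share of onsets could fall outside.** This needs two quantities that the documents do not give, so both are assumed and varied:

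- time from first to last lomustine dose: exponential, median 2 to 8 months, capped at day 336 and at death;
- radionecrosis onset after the end of radiotherapy: exponential, median 3 to 12 months;
- death: exponential with the planned experimental-arm median of 12.5 months (Statistical considerations and data management);
- end of radiotherapy on day 17.5 (mid-range start on day 3.5, plus 14 days).

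An onset counts only if it precedes death, and is inside the window if it occurs no later than 30 days after the last dose. Simulated share **outside** the window:

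| Median time on lomustine | Onset median 3 months | 6 months | 12 months |
|---|---|---|---|
| 2 months | 49% | 63% | 72% |
| 3 months | 40% | 54% | 65% |
| 5 months | 30% | 43% | 55% |
| 8 months | 22% | 35% | 47% |

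Ending radiotherapy on day 11 or day 20 instead moves the range to 20-70% or 22-73%.

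**3. Unobserved time alive.** Under the same survival and treatment assumptions, the share of time alive after the window closes is 65-82% over the whole of life, 29-62% over the first 12 months and 15-41% over the first 6 months. These are shares of time, not of events, and they depend heavily on the horizon.

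**4. Scale in patients.** Half of 411 is about 205. At the article's upper bound of 10%, about 20 patients would develop radionecrosis. Applying 22-72% gives 20 × 0.22 = 4.4 to 20 × 0.72 = 14.4, so roughly 4 to 14 outside the scheduled window. Because 10% is a ceiling, so are these counts.

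**The case against.** **The clock runs from the last dose, not from the end of radiotherapy.** This stands. Adverse events are assessed every 6 weeks throughout lomustine, for up to about a year, and the one-dose patient is the extreme case. If last dose is read to include radiotherapy, that patient is seen 23 to 37 days after it, which is still only weeks.

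**Most radionecrosis would be missed.** A reader might infer this, but the documents do not support it. They give neither onset nor time on lomustine, and under the assumptions above 28-78% of onsets fall inside the window. The 65-82% figure for lifetime person-time cannot stand in for a share of events.

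**Other routes may capture late events.** In part this stands. The article's general reporting rule (ICH GCP and EU Regulation 536/2014) has no stated end date, so serious or related late events may still reach the sponsor. But it is not a scheduled assessment, and the onward reporting the article describes centres on unexpected reactions, whereas radionecrosis is listed as expected. Follow-up cMRI is disease evaluation under RANO and is not marked after progression.

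**The article condenses a full protocol.** Late-toxicity reporting may be specified there. However, the article prints the calendar row by row, with adverse events in Table 5 and absent from Table 6, so the two need to agree in any case.

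**The arms are observed unequally in a way that hides experimental-arm harm.** A reader might infer this too. It is not shown: the closing rule is the same in both arms, and if radiotherapy delays progression, experimental patients are observed for longer.

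**The closing visit can precede the late blood counts.** The article says "Hematological toxicity, as the main concern in the treatment by lomustine occurs usually after 4 weeks after drug administration", and the closing visit may fall on day 23. But Table 5 schedules counts on days 28 and 35 of every cycle and nothing cancels them in the last one. This is a matter of wording.

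**Conclusion.** The gap in the schedule is read directly from Tables 5 and 6 and rests on no assumption: no adverse-event assessment is scheduled after 30 (±7) days from last dose, although the toxicity profile is a secondary objective and radionecrosis is its named main component. Given the treatment schedule, planned observation after radiotherapy varies from 3-26 days to 339-362 days with the number of lomustine doses (one to nine, full dose, no delays).

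The consequence is that late radionecrosis may be under-ascertained, chiefly in patients who stop lomustine early. Its size is not determined by the documents. The range of about 22-72% of onsets outside the window depends on the assumed onset and treatment-time distributions and on the planned 12.5-month median survival, and it ignores any capture through general safety reporting. The primary overall-survival analysis is not affected.

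**What to change.** - Add a row to Table 6, in both columns (with and without progression) and both arms, at the existing 12-weekly contacts. It should record radionecrosis of any grade and treatment-related events that are grade 3 or higher or serious.
- Report radionecrosis as cumulative incidence from randomisation, with death as a competing event, so that the estimate does not depend on how long lomustine was given.
- If the full protocol already requires late-toxicity reporting, reconcile Table 6 with it.
- Add one sentence stating how the 30 (±7)-day visit relates to the day 28 and 35 counts of the last cycle.

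The cost is an additional eCRF page and some extra data entry. No new visit or scan is needed, and treatment is unchanged.
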